**2022**

1. **Background**

Parkinson’s disease (PD) is a progressive neurodegenerative disorder characterized by motor and non-motor features. The disease progression is contributed by progressive denervation and neuro-degeneration of various areas in the brain and peripheral nervous system (Kouli et al. 2018; Poewe & Mahlknect, 2009). Clinically, this is demonstrated by increasing severity of motor features for example postural instability and freezing of gait following the evolution of poor responsiveness towards PD medications. Further, a wide range of non-motor disorders may develop and contribute significantly to disability experienced by PD patients (Kouli et al. 2018). Parkinson's disease is the fastest developing of the neurological illnesses that are currently the major cause of disability in the world. As the population ages and life expectancy rises, so does the cost of healthcare. Statistics of people suffering from PD will continue to increase, as does the duration of condition, resulting in greater PD sufferers in advanced stages (Ray Dorsey et al. 2018).

The global prevalence of PD based on the 2016 statistics is 6.1 million (Ray Dorsey et al. 2018). The global burden of PD in the same year is high, reported as 3.2 million disability adjusted life years (DALYs) with greater than 200,000 reported deaths. The burden of PD worldwide is expected to rise due to increased life expectancy of the ageing population, which increases the necessity for extended care (Ray Dorsey et al. 2018). The prevalence of PD in Malaysia as of 2016 statistics are 19 586 with death count as 514. The age-standardized rate of DALYs in Malaysia is estimated as 9694 with 19.1% increase from 1991(Ray Dorsey et al. 2018). This data is alarming as it is further reinforced by a report published by the Department of Statistics Malaysia in 2018, the number of people with Parkinson's disease in Malaysia is anticipated to increase fivefold by 2040, from an estimated 20,000 to 120,000 (Hassandarvish, 2019).

Mobility is defined as the capacity of people to transport from one place to another, in order to participate in the activities of daily living (ADL) in various settings and this is greatly affected in persons with PD. Limitation in mobility further causes devaluation amongst PD patients, followed by sadness and frustration (Bouca-Machado et al. 2020). A recent study by Zhao and colleagues (2020), reported in most dimensions, persons with PD demonstrated lower quality of life (QoL) than healthy controls, particularly in physical function and mental health. Given the deleterious impact of poor QoL on daily living and functional results, effective approaches to increase QoL in this population should be developed.

Similar trend is observed in Malaysia with the nonmotor aspect of PD greatly contributing to the decline in QoL in persons with PD as measured by Parkinson Disease Questionnaire-39 (PDQ-39 QoL). The caregivers' burden was also influenced by PDQ-39 QoL dimensions such as "mobility," "activities of daily life," "emotional well-being," and "stigma" (Rajiah et al. 2017). The progressive nature of PD with increasing disabilities imposes a significant burden to the patient's family, being the main caregiver. Literature documented high occurrences of depression and anxiety among the caregivers of persons with PD, which corresponds on the experienced caregiving burden (Mosley et al. 2017).

Further, PD poses a substantial economic burden. It is estimated that the cost of care in Asia for a person with PD range from 649 and 9544 Euro (€), with patients in home care had annual direct expenditures of 445 € per person while hospitalized PD persons had annual direct costs of 9,544 € per person (Maresove, Klimova & Kuca, 2017). In China, the average yearly cost per persons with PD is $3,225.94, with direct and indirect expenditures of $2,503.46 and $722.48, respectively. Estimated costs for persons with PD for surgery is $556.27, with appointment fees of $44.67, prescription medicine of $605.67, hospitalization costs $460.29, auxiliary examination costs $71.03, transportation costs $35.64, special equipment costs $10.39 and formal care costs

$719.50. Surgical therapy, dopamine agonist, and levodopa prices also contributes to the grand total (Yang & Chen, 2017). A recent study reported that family caregivers of persons with PD patients also experience income loss and are burdened with high cost of care throughout the care process (Martinez Martin et al. 2019).

Optimum PD management requires a multidisciplinary approach and participation from various health care professionals to address the multiple needs of the patient (van de Marck et al. 2009). However, family caregivers play the utmost vital role as they determine the final institutionalization and quality of care of the patient (Gultekin et al. 2017). This justifies the enforcement of family education and training from the early stage of PD to better equip family caregivers with the required knowledge and care skills as the disease progresses. Structured and comprehensive training program, consisting of all aspects of care, from multidisciplinary approach would enable the family to be better prepared for their role and minimize emotional and physical burden.

A review of the literature revealed that there are few studies that explored family training programmes. A study by Villasenor et al. (2020), examined the connections between family dynamics and sense of coherence, among PD family caregivers in Mexico and the United States.

The study concluded family dynamics play an important role in PD caregiver coping which improves caregiver comprehension, manageability, and significance. The study however, is a correlational study which provides preliminary evidence that a sense of coherence develops in similar ways across these cultures, and strengthens the needs of intervention focusing on family dynamics. A recent randomized controlled trial (RCT) by Bagheri et al. (2019) investigated the effect of a family-centered empowerment model on the burden of care among the caregivers of the older adults with PD. The authors indicated such a model will decrease the burden of care while improving the role of caregivers. The study further provides recommendations that carers of patients with chronic conditions should participate in family-centered empowerment initiatives. The family-centered empowerment model by Bagheri and co-researchers (2019), however focuses on patient education rather than therapy without incorporating any measures evaluating the effectiveness of such therapy on functional outcomes of persons with PD.

A quasi experimental study (Navratha Sanche et al. 2019) comparing the effects of a nine- week psychoeducational intervention and five-week education program on people with PD and their informal caregivers' QoL, psychosocial adjustment, and coping showed significant differences between groups for coping skills of patients and caregiver’s psychosocial adjustments. However, the intervention in the study by Navratha Sanche and co-researchers (2019) targeting both the persons with PD patients and caregivers are of psychosocial education and not physically related to coping skills during physical limitation of the patient. There were also no outcome measures evaluating the functional outcome of the PD patient, similar to the study by Bagheri et al. (2019).

A review (Kessler & Liddy, 2017) identifying the characteristics of self-management programs for persons with PD and the evidence for their effectiveness, identified 18 interventions. Only four of 18 interventions included caregivers or family members, thus indicating the lack of studies targeting family oriented intervention to address the need of persons with PD. Another developed program by Chaplin, Hazan & Wilson (2015), titled Hertfordshire Neurological Services Self-Management Programme is aimed to provide a module based program for neurological patients including persons with PD. The theoretical underpinnings of this module is social cognitive theory and self-regulation model, hence the module is based on education - problem solving goals minus the focus on the physical functions outcome improvement. Despite inclusion of caregivers, the module is not exclusive to PD but also stroke and multiple sclerosis.

A past study by A’Campo et al. (2010) evaluated a psychosocial education program named Patient Education Program for Parkinson (PEPP), which was developed by a consortium of experts from several European countries, with inputs from PD patients and their caregivers. The program aimed to assist PD patients and caregivers to adapt to the life changes triggered by PD. A total of 137 caregivers and 151 PD patients participated in the 8-week program. The researchers found that the education program was useful in improving the knowledge level and quality of life (QoL) of participants. A’campo et al. (2010) also proved the feasibility of such intervention to be executed in various countries. The drawback of the study is, similar to Chaplin, Hazan & Wilson (2015), there is no therapy based education program, as the intervention focuses on psychosocial without physical elements plus no functional outcomes were measured. The feasibility of such module is also limited to European countries.

While another study by Guo and colleagues (2009) reported that group education with personal rehabilitation was beneficial and fulfilled the long-term care needs of the PD population, it is not targeted to the family. The researchers included input from persons with PD and their caregivers in the formation of the educational program developed by a multidisciplinary team led by a neurologist. The program was well accepted by the caregivers who perceived it as useful in improving their knowledge, however the intervention is self-centered. Another RCT by Lewis et al. (2009) conducted a study to describe the Stress-Busting Program (SBP) for family caregivers and its effectiveness with three phases of intervention. The study reported significant decrease in perceived stress, depression, subjective caregiver burden, anxiety, and anger or hostility among caregivers. Caregivers also had improved general health, vitality, social function, and mental health scores. Similar to Guo et al. (2009), this intervention does not target to help caregivers cope with the physical limitation of PD patients, rather focused on reducing stress of caregivers.

All the programs published in reviewed studies (Hellqivst et al. 2020; Bagheri et al. 2019; Navratha Sanche et al. 2019; Kessler & Liddy, 2017; Chaplin, Hazan & Wilson, 2015; A’ Campo et al. 2010; Guo et al. 2009; Lewis et al. 2009) lack comprehensiveness as they delivered mainly education on PD and its care, without care skills training such as rehabilitation on the functional limitation. The programs' clinical and cost effectiveness were also not assessed, warranting further research to evaluate these aspects. With the expected rise in the number of PD patients in Malaysia (Hassandarvish, 2019), there will be greater demand on medical care and rehabilitation. However, despite this projection, local research on care and rehabilitation remains limited, with no research available to date on family training programs for the PD population in Malaysia. Two studies reported significant burden among caregivers of Malaysian PD population,

which is associated with the patients' advancing age, later stage of illness, presence of emotional disturbance and longer duration of care (Rosdinom et al. 2011, Rajiah et al. 2017). A recent local study (Vasanthi & Choo, 2021) reported that exercise in the presence of family and friends is a great facilitator for exercise. Similarly, Mosley et al. (2017) found that interventions by trained family caregivers at home assist in improving functionality and eventually quality of life, hence need to be included in the overall care program for PD. This justifies the need for a structured multi-component, sustainable and cost effective family training program for persons with PD. The summary of the literature review is attached in the table 1 literature review matrix.

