## Inclusion and exclusion criteria of participants

Table 2 Eligibility criteria of participants for needs analysis

| **Inclusion criteria** | **Exclusion criteria** |
| --- | --- |
| 1. 50-75 years old 2. Stage I and II of Parkinson’s disease based on HY scale 3. Availability of family caregivers. | 1. Impaired physical function due to other conditions such as a recent fracture within the past 6 months, severe arthritis or other neurological disease such as peripheral neuropathy. 2. Have medical illness limiting participation in exercise, such as unstable angina and   uncontrolled hypertension. |

Hoehn and Yahr scale used for screening the eligibility of participants (persons with PD) are attached in Appendix 2.

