## Eligibility Criteria INCLUSION CRITERIA:

1. PD patients
   1. Age 50-75 years old
   2. Stage I and II of Parkinson’s disease based on HY scale
   3. Availability of family caregivers.
2. Family caregivers
   1. Main caregiver who lives with the PD patient

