## Sampling Method and Sample Size Estimation

Eligible persons with PD will be recruited using a non-probability purposive sampling method. Selected participants (persons with PD) will then be allocated into either the test group (family-training program) or the control group (usual intervention) using simple randomization method. Sample size is calculated using Gpower software version 3.1. This study will use 6x2 Mixed Model Anova with post hoc analysis using Bonferroni. Therefore F-test (ANOVA repeated measures, within-between interactions) is chosen in Gpower software. Study power is set at 95%, alpha set at 0.05 and effect size of 0.41 was chosen based on the effect sizes for the primary outcomes of clinical interest from the study by Bueno et al. (2017). Based on sample size calculation, a total of 18 participants are required. Hence a minimum of nine PD patients and nine family caregivers (n=18 per group) will be recruited in each group which makes it a total of 36 participants in this study. Dropouts are not considered because intention-to-treat analysis will be used and all participants who are enrolled at baseline will be included in the final analysis.

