## Study Procedure

**(A) Recruitment and randomization**

Explanation about the study will be provided to participants as attached in the information sheet of appendix 11 and eligible persons with PD and family caregivers will be requested to sign an informed consent prior to participation in the study. Data on social-demography will be compiled and baseline measurements of functionality mobility and QOL of PD patients, caregiver knowledge, burden and QoL will be conducted and analyzed to ensure the two groups are comparable at baseline. The participants will then be randomly allocated into either the experimental group or the control group using ‘sealed opaque envelope’ technique by health personnel blinded to the study.

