## Statistical Tools

Statistical Analysis Statistical Package for Social Sciences (SPSS) will be used and variables will be analyzed descriptively, presenting mean and standard deviation. Intention to treat analysis will be performed. Effects of the interventions and comparison between groups will be analyzed using 6 x 2 Mixed Model ANOVA. The level of significance is set at *p*<0.05. Mixed model ANOVA will provide results for main effect of time (before and after therapies), main effect of group (experimental and control group), time and group interaction effect. Statistically significant main effect of time highlights significant changes in the dependent variables following interventions. Statistically significant main effect of group highlights the significant difference between experimental and control groups on the outcomes. Statistically significant time and group interaction effect highlights if experimental group yield the desired effect on dependent

variable significantly compared to control group (Field 2009). Besides aforementioned effects, partial eta squared (ηp²) will also analyzed to display the degree of influence of the independent variable. Cohen (1988) stated that the effect is large for ηp²≥0.14, medium for 0.14>ηp²≥0.06 and small for ηp²≤0.01. Comparison of costs of the two interventions will be done using independent samples *t* test. Statistical tests mapped to objectives in phase III is presented in Table 6.

Table 6 Statistical tests mapped to objectives for phase III

| **Objectives** | **Statistical test** |
| --- | --- |
| To compare the pre and post score of functions, mobility and QOL between persons with PD receiving the structured multi-component family-training program and control group.  To compare the pre and post score knowledge, QOL and burden between family members of persons with PD receiving the structured multi-component family-training  program and control group. | 6x2 Mixed Model ANOVA |
| To evaluate the cost effectiveness of the structured multi-  component family-training program and control group. | Independent sample *t* test |
| To determine the sustainability of the structured multi- component family-training program among the family of  persons with PD. |  |
| - Retention of effect | 6x2 Mixed Model ANOVA |
| - Compliance - Adherence - Drop outs | Descriptive statistics (Mean, standard deviation and percentage) |

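### Disease stage is linked to caregiver burden and known at entry, but 18 dyads are allocated by simple randomisation, leaving roughly a 15–24% chance of a stage gap of a third or more between arms

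*Protocol*

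**What the plan says.** The Background of the Protocol cites two studies of Malaysian caregivers in which burden was associated with the patients' "advancing age, later stage of illness, presence of emotional disturbance and longer duration of care". Caregiver burden is one of the trial's outcomes (Table 3).

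The Phase III inclusion criteria require "Stage I and II of Parkinson’s disease based on HY scale", so each patient's stage is established before allocation.

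Under Sampling Method and Sample Size Estimation (Phase III), participants are "allocated into either the test group (family-training program) or the control group (usual intervention) using simple randomization method". On numbers, the same section says: "Hence a minimum of nine PD patients and nine family caregivers (n=18 per group) will be recruited in each group". That is nine dyads per arm and 18 dyads in all. Sealed opaque envelopes are to be used; no blocking or stratification is stated.

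Under Recruitment and randomization, sociodemographic data and baseline outcome measurements "will be conducted and analyzed to ensure the two groups are comparable at baseline". The sentence comes before the allocation step. It names no test and does not list stage.

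Statistical Tools plans a mixed ANOVA with time, group and their interaction, names no covariate, and adds: "Statistically significant main effect of group highlights the significant difference between experimental and control groups on the outcomes".

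**The concern.** The Protocol identifies a patient characteristic related to one of its outcomes and records it before allocation, then does not use it in the allocation. With nine dyads per arm, chance alone can leave the arms noticeably different in stage. The safeguard offered is an analysis of baseline data. Such an analysis can describe imbalance but cannot prevent it, and if it takes the form of a significance test it has almost no power at this size.

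What is at stake is the group main effect. It averages over all visits, including the one before treatment, and the Protocol reads it as a difference between the interventions. A stage gap present at entry goes straight into that term. Allocation is also the one part of this that cannot be mended later: an analysis plan could add a covariate, but it cannot stratify an allocation already made.

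**Working it through.** **Inputs from the Protocol.** 18 dyads, nine per arm; simple randomisation; three visits (week 0, week 12, 6-month follow-up); f = 0.41, alpha 0.05, power 95%, sized on the within-between interaction.

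**Assumptions, not in the Protocol.** The number K of stage II patients among the 18, taken as 6 to 12; Fisher's exact test at 0.05 as the form of the baseline check; a stage II minus stage I difference of 0.5 to 1.0 SD; correlation 0.5 between visits.

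**1. The stated sample size.** With two groups, three visits, correlation 0.5 and sphericity, λ = f²·N·m/(1 − ρ) = 0.41² × 18 × 3/0.5 = 18.15, on 2 and (18 − 2) × 2 = 32 degrees of freedom. Power is 0.962. N = 17 just reaches 0.95, and equal arms make it 18. The figure of 18 therefore reproduces for the interaction.

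**2. Chance of a stage gap of 33 points or more.** Each dyad goes to either arm with probability 1/2. The probability of a stage II and b stage I dyads in the first arm is C(K, a)·C(18 − K, b)/2¹⁸. Summing over outcomes where the stage II proportions differ by at least 1/3:

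| Stage II among 18 | Simple randomisation | Arms held at 9:9 |
|---|---|---|
| 6 or 12 | 0.152 | 0.131 |
| 9 | 0.239 | 0.347 |

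If K is itself random with a 50% share, unrestricted simple randomisation gives 0.20.

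**3. Would a significance check see it?** For 6/9 against 3/9, Fisher p = 0.347. At nine per arm no gap below 5 of 9 (56 points) reaches p < 0.05: 0 v 5 gives 0.029, 1 v 6 gives 0.0498, and no gap of 4 is significant. With K = 9 under simple randomisation, 0.218 of the 0.239 (91%) would go unflagged; with K = 6 or 12, 0.124 of 0.152 (82%).

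**4. Effect on the group main effect.** A one-third gap times a stage effect of 0.5, 0.8 or 1.0 SD shifts the arm difference by 0.167, 0.267 or 0.333 SD. The variance of a three-visit mean is (1 + 2 × 0.5)/3 = 0.667, so the standard error of the arm difference is √(0.667 × 2/9) = 0.385 SD. On 16 degrees of freedom, the conditional two-sided rejection rate with no treatment effect is 6.9%, 10.0% or 12.9%, against a nominal 5%. These rates apply given such a gap; they are not the trial's overall type I error.

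**5. Effect on the interaction.** If stage adds the same amount at every visit, it drops out of all within-dyad changes and hence out of the time-by-group interaction. It enters only if stage I and stage II patients, or their caregivers, change at different rates. The Protocol gives nothing from which to size that.

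**6. After stratified blocking.** In a simulation of 40,000 runs at a 50% stage II share, a gap of 33 points or more never occurred. The largest gap was 11 points with blocks of 2 and 20 points with blocks of 4. With blocks of 4 and a total of 18, the arms differ by at most two dyads: for example, strata of 9 and 9 each leave one dyad over, and strata of 10 and 8 leave two over in one stratum.

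**The case against.** The strongest reply is that nothing here is wrong. Simple randomisation is valid, and the test keeps its type I error over repeated trials. The trial is sized on the interaction, from which a constant stage effect cancels. The Protocol reports an association with burden only, as one of four factors, and the trial admits only stages I and II, so the effect within that range is unknown. Covariates may be set in an analysis plan that is not shown. Small blocks also make late allocations easier to guess where dyads and trainers know the arm.

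Most of this stands, and it fixes the size of the point. It does not reach the allocation method, which the Protocol itself chooses, nor the claim that analysing baseline data ensures comparability.

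Three stronger readings are tempting, and the documents support none of them:

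- A reader might infer that a large stage imbalance is likely. At 15–24% under the stated method it is a real possibility, but not the expected outcome.
- A reader might infer that stage determines burden. The Protocol says only that the two are associated.
- A reader might infer that an imbalance is bound to pass the planned check. The Protocol names no test and does not list stage, so the Fisher result shows only what a significance test would do. A plain reading of 6/9 against 3/9 in a baseline table would reveal the gap.

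**Conclusion.** The point holds as a design improvement. Under the stated method, a stage gap of 33 points or more has a probability of about 0.15 to 0.24 if one third to two thirds of patients are stage II, and a significance test would miss 82–91% of such gaps. The group main effect is exposed: given such a gap, its false-positive rate would be about 7–13% if stage II carries 0.5 to 1.0 SD more burden. That stage effect and the stage mix are both assumptions. The interaction is affected only if the two stages change at different rates. There is no error of validity. Since the allocation cannot be redone once made, the change is worth making before recruitment.

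**What to change.** - **Sampling Method and Sample Size Estimation (Phase III).** Replace simple randomisation of dyads with permuted blocks stratified by Hoehn and Yahr stage (I, II), using two sets of the sealed opaque envelopes already planned. Use a block size such as 4, or varied sizes, and do not disclose it to those who recruit.
- **Statistical Tools and Table 6.** Keep stage as a factor in the between-group analysis so that it matches the allocation. This part is secondary, since an analysis plan may already provide for it.
- **Recruitment and randomization.** Describe baseline balance, including stage, after allocation, in place of an analysis intended to ensure comparability.

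Cost: a second set of envelopes, a few sentences, and one of 16 between-dyad error degrees of freedom. With blocks of 4, arms may differ by up to two dyads, and late allocations within a block become somewhat more predictable in a setting where the arm is known to dyads and trainers. Varied, undisclosed block sizes reduce that predictability.
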